### Statistical methods

Analysis will be done according to the intention to treat principle and the non-inferiority principle to show that imiquimod is not worse than an existing treatment (LLETZ). To investigate efficacy we will perform a per protocol analysis (although this is not the primary outcome of the study). The primary outcome is the difference between the probability of regression in the LLETZ and the imiquimod arms. The expected difference (LLETZ-imiquimod) will be calculated together with the 95% Aggresti confidence interval. If the upper bound of the interval lies below the non-inferiority margin of 10% non-inferiority of the imiquimod treatment is assumed to be proved. Logistic analysis of potential confounders (age at diagnosis, CIN grade, number of previous treatments, smoking, HPV-subtype) will be performed. Analysis will be based on intention to treat protocol.

The prevalence and severity of side effects of imiquimod and LLETZ treatment, as documented according to Common Terminology Criteria for Adverse Events guidelines, will be presented as proportions and means with 95% confidence intervals. Differences in the rates of overall side-effects and severe side-effects between the imiquimod and LLETZ groups will be tested with a chi-square test. Disease recurrence rates, defined by abnormal cervical cytology, after 6, 12 and 24 months will be evaluated in adequately treated patients by use of multiple logistic regression analysis, after adjustment for age at diagnosis, CIN grade, smoking sexual behavior and HPV subtype.

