### Study objectives and outcome measures

The primary study objectives are:To evaluate the effectivity of vaginal application of imiquimod 5% in the treatment of recurrent or persistent CIN. The primary outcome measure is reduction to normal cytology of the cervix at 26 weeks after start treatment in imiquimod and LLETZ group.

Secondary study objectives and outcome measures are:To evaluate the effectivity of vaginal application of imiquimod 5% in the treatment of recurrent/residual CIN; reduction to absence of dysplasia in histology at 26 weeks as compared to baseline in the Imiquimod group.Evaluate of the effect of treatment on HPV DNA positivity of CIN lesions, by comparison of PCR HPV-DNA detection at cervical biopsies/cytology taken at 0 and 26 weeks.Establish the incidence and severity of side effects of LLETZ and imiquimod therapy.Review the Quality of life (QoL) in patients at 0 and 20 weeks and after 1 year by the following QoL questionnaires: RAND 36, QLQ-C30 and QLQ-CX24.Estimate the long term recurrence rate of CIN lesions measured by reduction to PAP1 by cytology examination at 6, 12 and 24 months after treatment. We will request the first outcome taken by the Dutch screening program for cervical cancer: cytology or HPV status will be obtained.

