### Interventions

Patients will receive verbal and written information about the study procedure. They have to sign an informed consent, where after patients are randomized into the intervention arm or the standard treatment:Intervention arm: Imiquimod treatment. Patients in this group have to insert imiquimod 5% cream intravaginally for 16 weeks.Standard treatment. A LLETZ procedure is performed according to the current guidelines.

Patients in the imiquimod treatment group will apply imiquimod 5% cream intravaginally during 16 weeks. One sachet contains 12,5 mg of imiquimod and is applied with a vaginal applicator. The application frequency is 3 times a week. Patients get instructions and administer the cream themselves, before bedtime. The patients are advised to take an intravaginal shower with an applicator the next morning in order to remove cream leftovers, followed by an external shower to remove any remains on the vulva. Anti-inflammatory drugs (paracetamol or NSAID) can be used in case of mild systemic drug-related side effects. If the local or systemic side effects persist or are severe, patients are advised to reduce the frequency of the imiquimod insertion, first twice weekly, subsequently once weekly. Imiquimod treatment is discontinued for maximum of a week in case of persistent side effects. In order to prevent pregnancy, patients are advised to use adequate contraception. Subjects should refrain from vaginal sexual intercourse during the nights that imiquimod is applied until the vaginal shower the next morning. After 10 weeks a colposcopy is performed to rule out disease progression. Biopsies are only performed in case of suspicion of invasive disease.

In the standard treatment group, patients will undergo a LLETZ procedure within 4 weeks after the diagnosis. Excision of macroscopic lesions and the transformation zone will be achieved by a monopolar loop electrode, preferably under local anaesthesia.

Treatment efficacy is evaluated at 26 weeks follow-up for both groups. The Imiquimod group will have a Pap smear and a colposcopy with diagnostic biopsies. Biopsies are performed at the initial CIN lesion site and at any other suspect site, with a minimum of two. In case of persistent or progressive disease, surgical excision is performed. The LLETZ group will have follow-up with cervical smears at 6, 12 and 24 months according to the current guidelines.

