### Withdrawal of individual subjects and replacement

A study subject can stop the study at any time without explanation, this will have no consequences. The investigator can decide to withdraw a subject from the study for urgent medical reasons, non-compliance with the study procedures or pregnancy. There will be no replacement for withdrawn individuals. In principal a LLETZ will be performed, since this is still the standard treatment for patients with recurrent or persistent CIN lesions.

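### Under intention to treat, a 26-week smear cleared by a LLETZ given after withdrawal counts as imiquimod regression, which biases towards non-inferiority

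*Protocol article*

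**What the plan says.** Four statements in the protocol article bear on this point.

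- **Endpoint** (Study objectives and outcome measures): "The primary outcome measure is reduction to normal cytology of the cervix at 26 weeks after start treatment in imiquimod and LLETZ group". Nothing is said about an excision performed before that smear.
- **Analysis set** (Statistical methods): "Analysis will be done according to the intention to treat principle and the non-inferiority principle", and later in the same paragraph "Analysis will be based on intention to treat protocol". A per-protocol analysis is planned with a subordinate role: "To investigate efficacy we will perform a per protocol analysis (although this is not the primary outcome of the study").
- **Decision rule** (same section): "If the upper bound of the interval lies below the non-inferiority margin of 10% non-inferiority of the imiquimod treatment is assumed to be proved". The rule does not ask the per-protocol result to agree.
- **Withdrawal** (Withdrawal of individual subjects and replacement): a patient may leave at any time, and "The investigator can decide to withdraw a subject from the study for urgent medical reasons, non-compliance with the study procedures or pregnancy". Withdrawn patients are not replaced. On their treatment the article says: "In principal a LLETZ will be performed, since this is still the standard treatment for patients with recurrent or persistent CIN lesions".

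The surgery planned for persistent or progressive disease is described under Interventions together with the 26-week evaluation. It follows the endpoint and is not at issue here.

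**The concern.** LLETZ is both the comparator and the default treatment after withdrawal. Imiquimod is self-applied for 16 weeks and the endpoint falls at week 26, so a patient can leave imiquimod and have a LLETZ well before the endpoint smear. LLETZ is a single procedure done within weeks of diagnosis, so switching runs almost entirely from imiquimod to LLETZ.

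Analysed as randomised, with only the smear result counted, a cervix cleared by LLETZ is scored as regression on imiquimod. In a superiority trial this makes the arms more alike and is conservative. In a non-inferiority trial it favours success. The Background gives the aim as finding out whether topical imiquimod is effective in these lesions. A result that partly reflects LLETZ answers a different question, and a false claim could displace an effective treatment for a precancer.

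**Working it through.** **Inputs from the article.** LLETZ regression is 63%, imiquimod 60%, the margin 10 points, alpha 5%, 174 per group, 20% loss to follow-up and a total of 433 (Sample size calculation). The 95% interval is from Statistical methods, where the method named is read here as Agresti-Caffo.

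**Inputs that are assumptions.** The article gives neither of these:
- *w*, the share of imiquimod patients who have LLETZ before week 26 and still have a 26-week smear;
- *r*, the share of those patients who would have cleared on imiquimod without LLETZ.

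**The plan's own figure.** With unpooled variance, 0.63 × 0.37 + 0.60 × 0.40 = 0.4731. At one-sided 5% and 80% power, n = 6.183 × 0.4731 / (0.10 − 0.03)² = 597 per group, not 174. The figure of 174 appears only if the 3-point difference is taken in imiquimod's favour: 6.183 × 0.4731 / 0.13² = 173.1, and 2 × 173.1 / 0.8 = 432.7, or 433. That is a separate matter. Here 174 serves only as the planned evaluable group size.

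**Bias.** If *p* is the regression rate on imiquimod without LLETZ, then

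observed imiquimod rate = *p* + *w* × (0.63 − *r*).

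The added term is positive whenever *r* is below 63%. Its largest value, at *r* = 0, is 0.63 points for each 1% who switch. In that extreme, 10 / 0.63 = 15.9% switching offsets the whole margin.

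**False non-inferiority.** Set *p* = 53%, so that imiquimod is truly 10 points worse than 63%. For example, with *w* = 10% and *r* = 30%, the observed rate is 0.53 + 0.10 × 0.33 = 56.3%, a difference of 6.7 points. The table gives the exact binomial probability that the upper 95% Agresti-Caffo bound lies below 10%, with 174 per group.

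| Switching *w* | *r* = 53% | *r* = 30% | *r* = 0% |
|---|---|---|---|
| 0% | 2.6% | 2.6% | 2.6% |
| 5% | 3.2% | 5.1% | 8.8% |
| 10% | 3.9% | 9.2% | 22.6% |
| 20% | 5.8% | 24.3% | 69.2% |

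**Does the per-protocol analysis catch it?** Not reliably. Suppose 80% of the imiquimod arm completes with 63% regression, and the other 20% switch and would all have failed.
- Success on imiquimod itself is 0.80 × 0.63 = 50.4%.
- Observed intention to treat gives 0.504 + 0.20 × 0.63 = 63%, which passes 49% of the time.
- Per protocol compares 63% in about 139 completers (0.80 × 174) with 63% in 174 LLETZ patients, which passes about 45% of the time.

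Excluding the switchers removes likely failures, so the per-protocol set carries much the same bias.

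**The case against.** The strongest objection is that the key step is not in the text. The withdrawal section concerns patients who leave the study, and nothing says they attend a 26-week smear after LLETZ. How withdrawn or missing patients are scored is commonly left to a full protocol or analysis plan, neither of which is shown. This limits the point: the bias by this route needs that smear. But the article itself fixes the endpoint, the analysis set, the decision rule and the treatment after withdrawal. For a patient who does have the smear, those four leave only one reading.

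Second, following patients as randomised whatever treatment comes later is a recognised question. That is so, but the stated aim is the effect of imiquimod, and here the later treatment is the comparator itself.

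Third, the effect may be small. If imiquimod works as planned and switchers would also have cleared at 60%, 20% switching moves the rate only from 60% to 0.8 × 0.60 + 0.2 × 0.63 = 60.6%, and the chance of passing from about 27% to 31%. That stands, which is why the size is given as a range.

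A reader might go further in four ways that the documents do not support.
- *Stopping for side effects or progression leads to early LLETZ.* The withdrawal section names neither. Interventions answers side effects with less frequent application and a short pause. The week-10 check ("After 10 weeks a colposcopy is performed to rule out disease progression") has no LLETZ rule attached.
- *About 20% will switch.* The 20% in the sample size section is loss to follow-up, not switching.
- *Non-inferiority would be declared 49% of the time instead of under 1%.* That is the example above. It needs 20% switching and every switcher failing on imiquimod.
- *The per-protocol analysis would expose the problem.* In that same example it does not.

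**Conclusion.** The concern holds in a conditional form. As written, the primary analysis credits LLETZ clearance to imiquimod for any imiquimod patient who has LLETZ before week 26 and is still assessed then. The direction is towards non-inferiority as long as those patients would have cleared less often than 63% on imiquimod.

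The size cannot be fixed from the article. With imiquimod truly at the margin, the false-claim rate of about 2.6% rises to 3.2–8.8% at 5% switching, 3.9–22.6% at 10% and 5.8–69% at 20%. The upper ends assume that every switcher would have failed, and the lower ends that switchers would have done as well as the rest of the arm (53%). All figures assume 63% clearance after LLETZ in switchers, 174 assessed per group and a 95% Agresti-Caffo interval. If withdrawn patients have no 26-week smear, this route does not arise, and the result then depends on the missing-data rule, which the article does not give.

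**What to change.** 1. In the primary intention-to-treat analysis, count as non-regression any patient in either arm who had an excision beyond the allocated treatment before the 26-week smear.
2. Handle missing 26-week smears by one stated rule applied equally to both arms. A rule that turned missing smears into failures in the imiquimod arm alone would build in a bias the other way.
3. Report the as-observed intention-to-treat result as a sensitivity analysis.
4. Report the planned per-protocol analysis against the same 10% margin, as supportive evidence that should agree before non-inferiority is claimed. State that per protocol alone does not remove this bias.
5. Report the number and timing of excisions before week 26 by arm, so that readers can judge the size.

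The change is to analysis wording only, and patient care is unchanged. The cost is that the margin becomes somewhat harder for imiquimod to meet. Switchers who would have cleared anyway are counted as failures, which lowers the arm's rate by *w* × *r*, for example 0.10 × 0.30 = 3 points. Some power is lost if many switch.

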### Sample size calculation

The regression rate of a second LLETZ procedure is estimated 63% in a retrospective cohort (data not published). The regression rate of CIN lesions after treatment with imiquimod was based upon the only study reporting on the regression rate after 16 weeks of imiquimod therapy of primary CIN. This study showed a regression rate of 73% in patients with primary CIN lesions [23]. Since the effect could be lower in patients with residual or persistent CIN, we estimated the regression rate to be 60%.

To calculate the required sample size in this two-proportions non-inferiority trial we assume that the probability of regression is 63% for the standard (LLETZ procedure) while it is 60% after treatment with imiquimod.

Using a non-inferiority margin of 10% for the difference in proportions and a significance level (alpha) of 5%, a sample size of 174 per group is required to obtain a power of at least 80%. Allowing for 20% loss to follow-up the total required sample size is 433.

Because the uncertainty in the assumptions an interim analysis for futility will be performed by the Data Monitoring Committee (DMC) as soon as the primary outcome is available for 35 patients. This interim analysis is based on predictive power. That is the predicted probability of being able to prove non-inferiority given the results at the interim analysis. When the predictive power at this point is below 20% the trial will be stopped due to futility. Of course the DMC can always stop the trial due to safety concerns. The trial will never be stopped prematurely for efficacy so no alpha-adjustment is made.

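### 174 per group matches a one-sided 5% test, but non-inferiority is judged on a 95% interval (one-sided 2.5%), so the planned test has less power than the test that was sized

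*Protocol article*

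**What the plan says.** The Sample size calculation section sets the margin and level with "Using a non-inferiority margin of 10% for the difference in proportions and a significance level (alpha) of 5" per cent. It does not say whether that level is one-sided or two-sided. The assumed rates are that "the probability of regression is 63% for the standard (LLETZ procedure) while it is 60% after treatment with imiquimod", and the result is that "a sample size of 174 per group is required to obtain a power of at least 80" per cent. The total follows: "Allowing for 20% loss to follow-up the total required sample size is 433".

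The Statistical methods section fixes the analysis: "The expected difference (LLETZ-imiquimod) will be calculated together with the 95% Aggresti confidence interval". The decision rule is: "If the upper bound of the interval lies below the non-inferiority margin of 10% non-inferiority of the imiquimod treatment is assumed to be proved". Nothing in the article calls this interval one-sided or relates its level to the alpha used for sizing.

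The Sample size calculation section also provides a futility look once 35 patients have the primary outcome. It is based on the predicted probability of proving non-inferiority, with a stopping threshold of 20%.

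**The concern.** Only one bound of the interval decides the trial. With an ordinary two-sided 95% interval, that bound sits 1.96 standard errors from the estimate, which is a one-sided 2.5% test. If the sample size was worked out with 1.645 (one-sided 5%, matching a 90% interval), the test that was sized is not the test that will be run.

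Three things are at stake:

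- The stated power would not belong to the stated decision rule.
- A result whose 90% bound is below 10% and whose 95% bound is above it would fail under Statistical methods, yet could be argued to succeed under the level used for sizing.
- The interim futility calculation needs a definition of proof, and the predicted probability depends on which bound supplies it.

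**Working it through.** **Inputs.** From Sample size calculation: LLETZ 0.63, imiquimod 0.60, margin 0.10, alpha 5% (sidedness not given), power 80%, 174 per group, 20% loss, total 433. From Statistical methods: 95% interval, upper bound of LLETZ minus imiquimod compared with 0.10.

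**Formula.** Unpooled variance, equal groups: n = V × (z_alpha + z_power)² / D². Here V = 0.63 × 0.37 + 0.60 × 0.40 = 0.4731, and D is the margin minus the true difference (LLETZ minus imiquimod).

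- One-sided 5%: (1.645 + 0.842)² = 6.183
- One-sided 2.5%: (1.960 + 0.842)² = 7.849

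**Reproducing 174 and 433.**

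| Difference assumed | D | n, one-sided 5% | n, one-sided 2.5% |
|---|---|---|---|
| As written (LLETZ 63%, imiquimod 60%) | 0.07 | 597 | 758 |
| Equal rates of 63% (V = 0.4662) | 0.10 | 289 | 366 |
| Reversed (LLETZ 60%, imiquimod 63%) | 0.13 | 173.08, so 174 | 219.72, so 220 |

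Of the combinations tried, only one-sided 5% with the reversed difference gives 174: 0.4731 × 6.183 / 0.0169 = 173.08. The total follows from the unrounded figure: 2 × 173.08 / 0.8 = 432.7, so 433. Both printed figures come out together.

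**Power at 174 per group.** Power = Φ(D / SE − z_alpha), with SE = √(V / 174).

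- Reversed difference: SE = 0.05214 and D / SE = 2.493. Minus 1.645 gives 80.2%; minus 1.960 gives 70.3%.
- As written: D / SE = 1.342. Minus 1.645 gives 38.1%; minus 1.960 gives 26.8%.
- Equal rates of 63%: SE = 0.05176 and D / SE = 1.932. Minus 1.645 gives 61.3%; minus 1.960 gives 48.9%.

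**Exact check.** All binomial outcomes at 174 per group were enumerated, taking the named interval to be the Agresti-Caffo form (one success and one failure added per arm).

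| LLETZ / imiquimod | 90% interval | 95% interval |
|---|---|---|
| 60% / 63% | 80.4% | 70.3% |
| 63% / 60% | 38.4% | 26.8% |
| 63% / 63% | 61.4% | 49.0% |
| 63% / 53% (at the margin: type I error) | 5.2% | 2.6% |

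**No loss to follow-up.** With 216 per group (433 / 2, rounded down), exact power under the 95% rule is 79.4%, 32.2% and 58.1% in the first three rows. All three are still below 80%.

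**The case against.** Four arguments can be made for the plan.

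1. **The wording does not conflict on its face.** Under the ordinary two-sided convention, an alpha of 5% and a 95% interval agree. This stands. The one-sided reading is inferred from the numbers, and what disagrees with the decision rule is the figure of 174, not the sentence about alpha. The inference is strong because 174 and 433 both follow from it, and none of the combinations tried at one-sided 2.5% gives 174.

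2. **Power can still exceed 80%.** A reader might infer that the planned test falls short of the stated power whatever the true rates are. The document does not support that. With LLETZ at 63%, power under the 95% rule at 174 per group is about 81% if imiquimod reaches 67.5%, and 98% at 73%, the rate the article cites for primary CIN. What holds in general is narrower: at the same rates, the 2.5% test has less power than the 5% test. The article itself assumes 60% for imiquimod, not 67.5% or more.

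3. **The mismatch is conservative.** A reader might infer that a non-inferiority claim would be unsound. It would not be: the 95% rule holds type I error near 2.5%, and the interval itself needs no change.

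4. **The direction of the difference is the larger defect.** This also stands. At the stated rates, power is already only 38% at one-sided 5%. But correcting direction alone leads to 597 per group, which is still too few for the 95% rule (758), and correcting the level alone leads to 220, which does not give 80% power at the stated rates. Both need correcting, in one calculation.

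**Conclusion.** The point holds in this form. The sample size corresponds to a one-sided 5% test with the 3-point difference taken in imiquimod's favour, while the decision rule is a one-sided 2.5% test. The claimed power of at least 80% is therefore not the power of the planned test, either in the scenario that generates 174 or at the rates the article states. The level mismatch alone costs about 10 to 12 percentage points in the three scenarios examined.

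The conclusion rests on three assumptions: the 95% interval is two-sided, the sizing level was one-sided (inferred, not stated), and the interval is of the Agresti-Caffo type. The third matters little, because the normal approximation gives nearly the same figures. The stated power needs correcting before the trial relies on it, but this is a loss of power and a level left open, not an inflated risk of a false non-inferiority claim.

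**What to change.** - **Statistical methods:** keep the 95% interval and say that it is two-sided.
- **Sample size calculation:** give the level as one-sided 2.5% (two-sided 5%). Restate the power of 174 per group under the 95% rule, in the same recalculation that corrects the direction of the 63% and 60% rates. At those rates the figure to print is 27%. To keep 80% power there, about 758 per group is needed, or 2 × 757.82 / 0.8 = 1,894.5, so about 1,895 in total with 20% loss.
- **If one-sided 5% is truly intended:** name the 90% interval in Statistical methods before any data are seen. Power at the stated rates is then 38%, and 597 per group would be needed for 80%.
- **Interim analysis:** define proof of non-inferiority for the predictive power by the same bound as the final analysis.

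The text changes are a sentence or two in each section. The real cost is a much less favourable stated power or, if 80% is to be kept at the stated rates, a far larger trial. Moving to 220 per group (about 550 in total) would fix the level only for the reversed difference and should not be presented as the remedy.

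### The valid but unadjusted non-inferiority test leaves unused the modest precision available from five baseline covariates the plan already names

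*Protocol article*

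**What the plan says.** The Statistical methods section of the Protocol article takes as its primary quantity the difference between arms in the probability of regression. For the estimate it says "The expected difference (LLETZ-imiquimod) will be calculated together with the 95% Aggresti confidence interval". Imiquimod is declared non-inferior if the upper bound lies below 10 points. The Sample size calculation section puts the margin on the same scale: "Using a non-inferiority margin of 10% for the difference in proportions".

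Covariates enter in the next sentence of Statistical methods: "Logistic analysis of potential confounders (age at diagnosis, CIN grade, number of previous treatments, smoking, HPV-subtype) will be performed". The article does not say whether treatment arm is in that model, which effect measure it will report, or how its result relates to the margin. The later analysis of recurrence at 6, 12 and 24 months, by contrast, is expressly adjusted for a similar covariate list.

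**The concern.** Margin, estimate, interval and decision rule all sit on the risk-difference scale, and no covariate enters any of them. The article names the estimator, the interval and the rule, so leaving the decisive test unadjusted is a stated choice. The covariates are nevertheless thought relevant enough to list, and a model for them is planned.

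The article calls them potential confounders. In a randomised intention-to-treat comparison, baseline variables differ between arms only by chance. Their main use is to absorb outcome variation and correct chance imbalance, which narrows the interval. A separate logistic analysis does this for the non-inferiority question only if its result is brought back to the scale of the margin. At stake is some precision in a trial that, under its own assumptions, has little to spare.

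**Working it through.** **Inputs from the Sample size calculation section.** The plan assumes that "the probability of regression is 63% for the standard (LLETZ procedure" arm, "while it is 60% after treatment with imiquimod". The true LLETZ-minus-imiquimod difference is therefore +3 points. The margin is 10 points, alpha is 5% with no sidedness stated, and there are 174 women per group. The 95% interval in Statistical methods corresponds to one-sided 2.5%.

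**The plan's own figure.** The article states that "a sample size of 174 per group is required to obtain a power of at least 80" per cent. The usual formula is n = (z_alpha + z_beta)² × [p1(1−p1) + p2(1−p2)] / distance², with variance term 0.63×0.37 + 0.60×0.40 = 0.4731.

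- Distance 0.10 − 0.03 = 0.07, one-sided 5%: 6.183 × 0.4731 / 0.0049 = 596.9, so 597 per arm.
- Distance 0.07, one-sided 2.5%: 7.849 × 0.4731 / 0.0049 = 757.8, so 758 per arm.
- Distance 0.10 + 0.03 = 0.13, one-sided 5%: 6.183 × 0.4731 / 0.0169 = 173.08, so 174 per arm. Then 2 × 173.08 / 0.8 = 432.7, so 433.

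The stated 174 and 433 were reproduced only by the third route, in which the 3-point disadvantage has its sign reversed. That is a separate problem. It matters here because it sets the baseline power.

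**Power without and with adjustment.** Power = Φ[(0.10 − d)/SE − 1.96], with SE² = (1 − R²) × variance term / 174. R² is the proportional variance reduction from the covariates and is assumed.

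| R² | 63% v 60% (d = 0.03) | 63% v 63% (d = 0, variance term 0.4662) |
|---|---|---|
| 0 | SE 0.0521, power 26.8% | SE 0.0518, power 48.9% |
| 2% | SE 0.0516, power 27.3% | SE 0.0512, power 49.7% |
| 10% | SE 0.0495, power 29.3% | SE 0.0491, power 53.0% |
| 20% | SE 0.0466, power 32.3% | SE 0.0463, power 57.9% |

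A reduction of 2 to 10% is worth 174/0.98 = 178 to 174/0.90 = 193 women per arm. For 80% power at 63% v 60% with the 95% interval, the number needed per arm falls from 758 to 743 (R² 2%) or 683 (R² 10%).

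**Is 2 to 10% plausible?** Two simulations at 174 per arm compared the unadjusted difference with a logistic model standardised to a risk difference. One used two assumed sets of covariate effects and gave variance reductions of about 2% (weak) and 10% (moderate). The other used a single covariate score with standard deviation 0.3, 0.5, 0.7 or 1.0 on the log-odds scale and gave about 3%, 5%, 9% and 15%. In the second, the unadjusted and standardised estimates both averaged about 3 points, so standardising changes the precision and leaves the target unchanged.

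**Scale.** The odds ratio (imiquimod to LLETZ) that equals a 10-point loss depends on the LLETZ rate: 0.667 at 50%, 0.662 at 63%, 0.619 at 75% and 0.529 at 85%. A conditional odds ratio therefore has no fixed reading against the margin, although between 50% and 63% the translation hardly moves.

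**The case against.** The strongest reply is that nothing here is wrong. Margin, estimand, interval and rule agree with each other, an unadjusted risk difference is valid under randomisation, and not adjusting is a legitimate choice. This stands as far as validity goes. What remains is avoidable imprecision in a test that the article itself fixes.

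A reader might infer that the logistic analysis yields odds ratios that cannot be set against the 10-point margin, and so competes with the primary result. The document does not support this. It never mentions an odds ratio and does not say that arm is in the model. A condensed article may leave the effect measure to the full plan, and the same logistic model can be standardised to a risk difference.

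The gain is also small and rests on assumed covariate strength. That stands, and it limits the claim. A very prognostic score could do better, but even a 20% reduction gives only 32.3% power at 63% v 60%.

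Finally, a new primary estimator touches the futility rule, and a model with arm and five covariates would be unstable on 35 patients. That is correct, and it is met by leaving that look unadjusted.

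**Conclusion.** The point holds as one of precision. The decisive test is unadjusted and valid, and the covariates already named for a separate model could narrow its interval on the scale of the margin. On an assumed variance reduction of 2 to 10%, the gain is about 0.5 to 2.5 points of power at 63% v 60% (26.8% to 27.3-29.3%), or about 0.8 to 4.2 points if both arms are 63% (48.9% to 49.7-53.0%). These figures assume 174 evaluable women per arm and the 95% interval.

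Two stronger readings should be resisted. The unadjusted analysis is not biased and does not inflate type I error. Nor does adjustment rescue the sample size: with 758 per arm needed at 63% v 60% and 174 planned, that problem needs its own correction. The change is worth making because it costs little.

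**What to change.** State in Statistical methods, before outcomes by arm are seen, that:

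- the primary estimate comes from the planned logistic model with arm, age at diagnosis, CIN grade, number of previous treatments, smoking and HPV subtype in prespecified groups;
- predicted probabilities are averaged over all randomised women under each arm, giving a LLETZ-minus-imiquimod risk difference with a 95% interval (delta method or bootstrap);
- the upper bound of that interval is held against the same 10 points;
- the unadjusted Agresti interval is reported as supportive;
- the futility look at 35 patients stays unadjusted.

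Describe the covariates as prognostic rather than as confounders.

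The cost is a little more programming and two rules to settle in advance: how HPV subtypes are grouped and how missing covariate values are handled. No extra patients are needed. Age, smoking, medical history and HPV genotype are on the baseline data list, and CIN is histologically confirmed at entry. Number of previous treatments is not listed separately, so the case report form should be checked to confirm that it is captured.
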